**Figure 1 F1:**
[figure not shown]
Study power curve to detect a 10 nmol/L increase in the primary outcome (SHBG) for different standard deviations of the between-group difference in the change from baseline.

### Randomization

2.4

The patients will be randomly assigned either to supervised physical exercise (exercise group; EG) or to a usual care control group (CG). A simple computer-generated randomization sequence^[60]^ will be obtained, representing the allocation of each participant. Individual allocations will be held into a sealed, opaque envelope and numbered in sequential order corresponding to the order in which the participants will be randomized. Each participant will be randomized (the corresponding envelope will be opened in front of the patient) at medical discharge following bariatric surgery, provided the participant has previously met the inclusion criteria, signed the informed consent, and performed baseline assessments (pre-test; Fig. 2). All study-related information will be stored securely at the study site. All laboratory specimens, reports, data collection, process, and administrative forms will be identified by a coded ID (identification) number to maintain participants’ confidentiality. All records that contain names or other personal identifiers, such as locator forms and informed consent forms, will be stored separately from study records identified by code number and only accessible by the principal investigators.

**Figure 2 F2:**
[figure not shown]
Graphical representation of the data-collection planning.

### Blinding

2.5

Due to the nature of the intervention (physical exercise), it is not possible to “blind” the patients, since they will inevitably know their allocation. However, the team that evaluates the primary and secondary outcomes, including the gynaecological tests, will be blinded to the patients’ allocation. The participants will receive explicit instructions not to disclose their allocation with the study staff. In addition, the data analysts will also be blinded to the patients’ allocation.

### Data collection

2.6

#### Assessment calendar

2.6.1

Figure 2 graphically represents the data-collection planning that each enrolled participant will complete throughout the study. All participants will complete the whole battery of assessments at three time points (i.e., at baseline or pre-test [T1], within ∼12 days before the surgery; week 16 or post-test [T2], within a margin of 3 to 12 days following the intervention completion; and 12 months or follow-up [T3], within a 15 day margin).

Each of the 3 full clinical assessments (pre-test, post-test, and 12-month follow-up) consists of 4 visits (Table 2). In addition, participants in both groups will continue their protocol of regular visits to the surgical and nutrition clinics during the study (months 1, 3, 6, and 12 after surgery), in which participants from both groups (EG and CG) will receive lifestyle recommendations including internationally accepted physical activity and nutrition recommendations.^[27]^

**Table 2 T2:**
[figure not shown]
Outline of the planned evaluations during each of the 3 full study assessments (pre-test, post-test, and follow-up at 12 months).

#### Data collection related to the primary study aim (ovarian function)

2.6.2

All the variables measured in serum will come from a blood sample (day 1 of assessment) taken in the morning (9:00) after a minimum of 12 h fasting. 20 mL of blood will be taken, which will then be processed, frozen and stored in a standardized way in the Public Health System of Andalusia Biobank (https://goo.gl/SbGFyd) for further analysis, thus guaranteeing the standardization and quality of the biological sampling process.

##### Primary outcome

2.6.2.1

The primary study outcome is the SHBG (nmol/L) since it is a fundamental hormone for ovarian function and ovulation, is inversely related to obesity and is likely to increase with weight loss and physical exercise. It will be measured in serum and analyzed by immunoassay using the Beckman Coulter kit (ref. A48617), with a maximum value of 200 nmol/L and an inaccuracy of <7%.

##### Secondary outcomes related to ovarian function

2.6.2.2

###### Serum markers

2.6.2.2.1

Anti-Müllerian hormone (AMH, ng/mL; kit's ref. B13127), follicle-stimulating hormone (FSH, mIU/mL; kit's ref. 33520), thyroxine (T4, ng/dL; kit's ref. 33880), thyrotropin (TSH, μIU/mL; kit's ref. B63284), LH (mUI/mL; kit's ref. 33510), estradiol (E2, pmol/L; kit's ref. B84493), prolactin (PRL, ng/mL; kit's ref. 33530) and total testosterone (T, nmol/L; kit's ref. 33560) will be measured by chemiluminiscence immunoassay (Beckman Coulter) according to manufacturer's protocols. Finally, free androgen index will be calculated as the total testosterone/SHBG ratio.

###### Markers obtained from a transvaginal ultrasound using Toshiba Xario ultrasound equipment (Toshiba Medical Systems Corporation, Japan) equipped with a 7 MHz curved endovaginal transducer

2.6.2.2.2

-Oocyte count. The total number of follicles of between 2 and 8 mm in size displayed on both ovaries will be recorded.-Ovarian volume: the longitudinal, oblique, and transverse axes are measured graphically in millimetres. The ovarian volume of each ovary is calculated with the following formula: volume = D1 × D2 × D3 × 0.52.^[61]^ Where D represents the longitudinal, oblique and transverse axes, respectively.-Endometrial thickness: the thickness of the endometrium (measured in millimetres) displayed ultrasonically in a longitudinal section of the uterus.-Uterine arterial pulsatility index (left, right, and middle), measured using ultrasound. The 7 MHz endovaginal transducer should be located paramedial to the uterine cervix at the level of the inner cervical opening. The vessel should be identified with colour Doppler using high speed scales (between 30 and 50 cm/s) to allow selective identification. The insertion angle for the measurements must be less than 45°. Three or more waves of similar characteristics should be obtained for the measurement, with adequate magnification, occupying at least three quarters of the screen. The size of the Doppler sample should be equivalent to the artery's diameter and placed in the centre of the vessel. The pulsatility index (PI) is then calculated.

###### Other outcomes relevant to the primary aim (ovarian function)

2.6.2.2.3

-The duration of menstrual bleeding (days) and menstrual cycles (days) will be obtained through interview.-Hirsutism. This will be measured using the Ferriman Gallwey Scale.^[62]^ The score will be: less than or equal to 8—normal; from 8 to 11—mild hirsutism; from 12 to 19—moderate hirsutism; and from 20 and above—severe hirsutism.

#### Data collection related to secondary aims

2.6.3

##### Markers of chronic inflammation and insulin resistance obtained from serum

2.6.3.1

-High-sensitivity C-reactive protein (hs-CRP) levels (mg/L), as a relevant indicator of systemic inflammation which is highly susceptible to decrease through physical exercise.^[63]^ This is performed by immunoturbidimetric analysis using the Beckman Coulter kit, with a detection limit of 80 mg/L and a coefficient of variation <1 mg/L.-Interleukin 6 (IL-6; pg/mL), tumor necrosis factor alpha (TNFα; pg/mL) and leptin (pg/mL) will be measured by immunoassay using specific kits according to manufacturer's protocols: Human IL-6 ELISA Kit High Sensitivity (abcam; ab46042), TNF alpha Human ELISA Kit (Thermo Fisher Scientific; KHC3011) and Leptin Human ELISA Kit (Thermo Fisher Scientific; KAC2281), respectively.-Glomerular sedimentation rate (GSR, mm/h). This will be measured using the Menarini Diagnostics reagent.-Glucose and insulin. Glucose and insulin will be measured by immunoassay using Cobas kit according to manufacturer's protocols. The HOMA (homeostasis model assessment of insulin resistance) will be calculated using the formula ([insulin, mIU/L] × [glucose, mg/dL])/405.^[64]^

##### Arterial stiffness and systolic, diastolic, and mean arterial blood pressure

2.6.3.2

Arterial stiffness will be measured through pulse wave velocity (PWV), the elevation of which is an early marker of arteriosclerosis.^[65]^ The Mobil-O-Graph 24 h pulse wave analysis monitor (IEM GmbH, Stolberg, Germany) will be used, the operation of which is based on the oscillometry recorded by a blood pressure sleeve placed on the brachial artery.^[66–68]^ This device has been shown to be reliable in measuring the PWV in different populations, measuring (in addition to arterial stiffness) the brachial and central blood pressure [both systolic (SBP) and diastolic (DBP)], as well as the resting heart rate in one single measurement.^[67]^ All these parameters will be measured in the same procedure and using the same device, in triplicate, in a seated position, after 5 min of rest, in a room that has a comfortable temperature, following international recommendations.^[65,69]^ Mean blood pressure (MAP) will be calculated using the formula MAP 1/3(SAP-DAP) + DAP.

##### Body composition and total weight loss

2.6.3.3

Body composition will be assessed by dual-energy X-ray absorptiometry (DEXA; DMS Imaging, STRATOS dR). The percentage of total and segmental body fat, fat-free mass and muscle mass will be measured. Weight (InBody 270) and height (Seca 213) will be measured. Total weight loss (in %) will be calculated as (pre-operative weight—follow-up weight/pre-operative weight) × 100].^[70]^ While in non-bariatric obese adult population, a total weight loss of 10% is usually the target ^[71]^, in the bariatric surgery population, a weight loss <20% at 12 months after the surgery is considered insufficient or suboptimal.^[70]^

##### Physical fitness

2.6.3.4

Cardiorespiratory fitness will be evaluated with the Bruce protocol^[72]^ on a treadmill, one of the most widely used tests worldwide to assess aerobic capacity.^[73]^ The lower limb muscular strength will be evaluated using the 30 s chair stand test,^[74]^ while the upper limb muscular strength will be evaluated using handgrip dynamometry.^[75]^ Finally, the back-scratch test will be performed to evaluate the range of motion of the shoulder and the shoulder girdle.^[74]^

##### Health-related quality of life

2.6.3.5

Health-related quality of life will be evaluated with the Spanish version of the 36-item Short Form Health Survey (SF-36 v2).^[76]^ The total score of each of the 8 subscales (and the physical and mental composite scores) ranges from 0 to 100, with high values representing a higher quality of life.

##### Sexual function

2.6.3.6

Sexual function will be evaluated using the Spanish version^[77]^ of the 9-item Female Sexual Function Index (FSFI),^[78]^ question questionnaire grouped into six domains: desire, excitement, lubrication, orgasm, satisfaction, and pain. The score of each item goes from 0–5 or 1–5, with low values representing a female sexual dysfunction.

#### Control variables and other variables to be recorded

2.6.4

Physical activity (PA) and sedentary time will be measured by accelerometry (ActiGraph GT3x+; ActiLife software version 6.11.7).^[79,80]^ In each of the 3 full assessments, patients will wear a triaxial accelerometer on the right hip for 24 h (except for bathing or water activities) that records acceleration in all three movement axes and provides results in min/day of physical activity of different intensities and sedentary time for 7 complete days. Based on the moderate-to-vigorous physical activity, we will determine whether participants meet (or not) the American College of Sports Medicine's minimum physical activity recommendations (≥150 min/week of moderate to vigorous physical activity).

Usual intake estimates of food groups, energy and nutrients: the self-administered food frequency questionnaire (FFQ) used in the PREDIMED study^[81]^ will be employed, along with 24-h reminders on 2 non-consecutive days.

Adherence to the Mediterranean diet will be measured using the questionnaire employed in the PREDIMED study.^[82]^

Sociodemographic variables: age, marital status, educational level, employment situation, income level, among others, will all be recorded ad hoc. Relevant data from clinical history, such as personal antecedents of obesity (duration of obesity), cardiovascular disease, hypertension, obstructive sleep apnoea (OSA), type 2 diabetes, or medication use, will be recorded.

Surgical technique: the surgical techniques performed will mainly be the one anastomosis gastric bypass (OAGB), and the laparoscopic sleeve gastrectomy (SG; only when BMI ≥ 50).

### Intervention

2.7

All the participants will continue their habitual care following bariatric surgery.

#### Experimental group (supervised exercise; EG)

2.7.1

Patients assigned to the EG will perform a 48-session supervised physical exercise program spread over 16 weeks with a frequency of 3 sessions per week and a volume of 1 hour per session. This distribution has proven applicable in patients undergoing bariatric surgery.^[83]^ The exercise program has been comprehensively described elsewhere^[84]^ following the Consensus on Exercise Reporting Template (CERT)^[58,85]^ to maximize transparency and replicability. The exercise program will combine muscle strength and aerobic exercise in the same session (called concurrent training). Concurrent training has shown to increase weight loss and improve body composition, muscle strength, aerobic capacity and bone-mineral density to a greater extent than aerobic training and separate strength training in patients obese dieting adults.^[86]^ The exercise program will comply with international guidelines^[87,88]^ for aerobic and strength training, following criteria to progress effectively and safely.^[58]^ The training sessions will be individual and will be held in the sports facilities at the University of Almería. All sessions will be supervised^[89]^ by a Personal Trainer with a Grade in Physical Activity and Sports Sciences, and either a Master Degree in Personal Training or >2 years’ experience training obese people.

The training sessions will consist of a 5-min warm up on a treadmill, a main section of 50 min (i.e., including compensatory exercises at three levels of difficulty, followed by concurrent training), and a 5-min cool-down with dynamic and static flexibility exercises. The main section will combine a strength training block and an aerobic training block, whose exercises will be progressively complex and intense in a personalized way over 4 main phases: the familiarization phase (week 1–4), phase 1 (weeks 5–8), phase 2 (weeks 9–10) and phase 3 (weeks 11–16) (Table 3). With regard to strength training, in the familiarization phase, exercises will be carried out to learn movement patterns, strength exercises using one's own body weight and with elastic bands,^[90]^ as well as exercises to adapt to power exercises using external weight in the following phases. Starting from Phase 1, exercises will be performed with external loads and the intensity of these loads will progress approximately from 50% to 75% of 1 Repetition Maximum (1RM) quantified by the character of effort (CE), that is, based on the maximum number of repetitions that the patient can perform with each load. There will be a total of 6 main resistance exercises (i.e. squat, seated lat pull-down, bench press, seated low row, push press with dumbbells, and deadlift) focused on large muscle groups and the main movement patterns. Patients will complete 1 serie of each exercise during the first weeks of phase 1 of the program and progress to 2 and 3 series in phases 2 and 3. Rests between series will be 30–60 s and the execution speed for the exercises will be the maximum possible in each repetition.^[89,91]^ With regard to aerobic training, continuous aerobic training will be performed starting in the familiarization phase with a volume of 15 min (at 65% of the Heart-Rate Reserve [HRR]) until reaching a volume of 25 min at 85% of the HRR in phase 3. Exercise intensity will be controlled with heart rate monitors (Polar V800 pulsometer) and the subjective Rating of Perceived Exertion (0–10 Borg) in the case of aerobic training, as well as the OMNI-Resistance Exercise Scale for strength training.^[92]^Table 3 represents the training program schematically.

**Table 3 T3:**
[figure not shown]
Training periodization.

##### Strategies to register and maximize adherence to the training program

2.7.1.1

Adherence to the exercise program will be measured throughout the intervention period on a record sheet designed *ad hoc* and completed daily by the personal trainer in each session. In addition to the attendance percentage ([no. of sessions attended/no. of sessions planned] × 100), other variables such as punctuality, physical activity outside of the program, the number and type of adverse events, and the compliance attitude during the session will also be recorded. The level of perceived effort, mood and sense of acute exhaustion induced by exercise will be recorded to try to anticipate possible symptoms (if any) of fatigue or dissatisfaction and to make pertinent adaptations (if needed). Since program adherence is essential to study the clinical effectiveness of the exercise program, strategies will be implemented to maximize it, such as sending motivational messages (each week) and videos (each month) via Whatsapp throughout the program intervention.^[84]^

#### Control/usual care group (CG)

2.7.2

All participants (both in the CG and EG) will receive the usual hygiene-dietary and healthy-cardio lifestyle recommendations in line with international guidelines.^[27]^ Patient's lifestyle following bariatric surgery is fundamental to its success, so all participants will receive both at the time of medical discharge and during post-operative visits (at 1, 3, 6, 9, and 12 months; see Fig. 2) advice based on the latest evidence-based clinical recommendations, jointly established by the American Association of Clinical Endocrinology, the Obesity Society, and the American Society of Bariatric and Metabolic Surgery.^[27]^

### Participant care during the follow-up (from T2 to T3)

2.8

From the end of the intervention (week 16; T2) until the 12-month follow-up assessment (T3; approximately week 52 after surgery), participants in both groups will receive exactly the same treatment, that is, their usual follow-up (see Fig. 2) following bariatric surgery. Between T2 and T3, the EG will not receive any additional information on physical activity, exercise, or any aspect as distinct from the CG. In this way, we will be able to study the medium-term effect (12 months) of the 16-week exercise program.

### Patient safety

2.9

For the entire study period, any possible adverse effects attributable to the intervention will be reported. An adverse effect in the EG is defined as any skeletal muscle injury that occurs during (or as a result of) the training performed.

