### Criteria for interrupting study participation

2.10

The number of participants interrupting participation, together with the reasons, will be registered and appropriately reported.

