#### Interrupting participation by the researcher

2.10.2

The research team may discontinue any patient's participation (a withdrawn participant) at any time, provided that their participation poses a risk to their safety or a violation of the study protocol. This can occur under the following circumstances:

-Severe skeletal muscle injury that alters one's normal lifestyle (as a consequence, or not, of participating in the study).-Pregnancy during the intervention period. Alterations in the hormonal profile that occurs during pregnancy would irredeemably affect the study results.-A change of residence, making all postoperative assessments impossible.-Death.

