### Study limitations/risks and contingency plan

3.1

Potential risk 1: EG patients do not attend the intervention.

Contingency plan: Different strategies will be implemented to maximize adherence to the exercise program. We will have a Contracted Personal Trainer with a Bachelor's or graduate degree in Physical Activity and Sports Sciences and a Master's in Personal Training, who has experience in training people with obesity. Each week, the EG participants will receive motivational messages via WhatsApp. In addition, at the start of each month, patients will receive a motivational video from the coaches and medical team through the same channels. The emotional state (The Feeling Scale) will be monitored and any adverse events that occur will be recorded during training. This will allow us to understand how they feel and offer alternatives.

Potential risk 2: Recruitment and/or retention rate are lower than planned.

Contingency plan: With the medical team involved, a large proportion of childbearing age women undergoing bariatric surgery in the province of Almería will be invited to participate in the study. If the rate of recruitment is not as expected, we would try to arrange new exercise training facilities (other than the University of Almería) in areas of the province where a greater number of participants could be included.

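### The adverse-effect definition counts only training-related muscle injury in the exercise group; it is narrower than the article's other harms statements and gives no basis for comparing harms between arms beyond withdrawals

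*Protocol article*

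**What the plan says.** The protocol article deals with harms in four places.

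- **2.9 Patient safety** opens with a broad promise: "For the entire study period, any possible adverse effects attributable to the intervention will be reported". The next sentence narrows it: "An adverse effect in the EG is defined as any skeletal muscle injury that occurs during (or as a result of) the training performed". No definition is given for the control group.
- **2.7.1.1 (adherence)** has the personal trainer complete a record sheet at every session. Among other items it covers "the number and type of adverse events". This is not limited to muscle injury.
- **3.1 (risks and contingency plan)** says, for the exercise group, that "any adverse events that occur will be recorded during training".
- **2.10 (interrupting participation)** says: "The number of participants interrupting participation, together with the reasons, will be registered and appropriately reported". This is not limited to one arm. Section 2.10.2 lists severe muscle injury of whatever cause, pregnancy during the intervention period, a change of residence and death as circumstances for withdrawal by the research team.

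Both arms also share clinic contacts. Section 2.6.1 says that "participants in both groups will continue their protocol of regular visits to the surgical and nutrition clinics during the study". Sections 2.6.1 and 2.7.2 describe these visits as occasions for advice and do not mention asking about adverse events.

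**The concern.** According to the Discussion, training starts immediately after bariatric surgery. Section 2.7.1 describes external loads rising to roughly 75% of one-repetition maximum and aerobic work rising to 85% of heart-rate reserve. In that setting the events of interest are not only muscular. Cardiac, metabolic, syncopal, wound and abdominal-wall events, and readmissions, all lie outside the stated definition.

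The definition also depends on attribution to training, so it cannot be applied to an arm that does not train. Women recovering from surgery may have complications whether or not they exercise. Without a control count, an excess or a deficit with exercise cannot be estimated.

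Two features of the trial raise the stakes. The main efficacy analysis (2.11) includes only participants who attend at least 80% of sessions, so a woman who stops attending because of an event can drop out of the main result. The Discussion also intends the trial to inform exercise prescription in this population. A published statement that few adverse effects occurred would be read in that light, although it might mean only that few muscle injuries occurred.

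**Working it through.** The article gives no figure for harms, so there is none to reproduce. The check sets the statements side by side and asks, for each kind of event, where it would be recorded and whether it would count under 2.9.

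| Event | Stated record | Counts under the 2.9 definition? |
|---|---|---|
| Exercise group: muscle injury in a session | Trainer's sheet (2.7.1.1, 3.1) | Yes |
| Exercise group: muscle injury from training that shows itself later | Reporting promised in 2.9, route not stated | Yes |
| Exercise group: non-muscular event in a session | Trainer's sheet (2.7.1.1, 3.1) | No |
| Exercise group: non-muscular event outside sessions or after week 16 | None, unless it leads to withdrawal (2.10) | No |
| Control group: any event | None, unless it leads to withdrawal (2.10) | No definition given |

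Three observations follow.

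1. **Scope conflict.** The first sentence of 2.9 and the records in 2.7.1.1 and 3.1 are open as to type of event; the second sentence of 2.9 is not. The third row shows the result: an event can be written down and yet not be an adverse effect. The article does not say which statement governs reporting.
2. **Period conflict.** Section 2.9 speaks of the entire study period, but the only described log is tied to training sessions. These end at week 16, and under 2.8 both groups then receive identical usual follow-up until T3.
3. **Arm.** Withdrawals are the only harms-related information stated without restriction to the exercise group. They miss any event that does not end participation. Section 2.10.1 also lets a woman leave without giving an explanation, so the reason may be unknown.

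**What a full comparison could deliver.** Section 2.3 gives 36 women plus a 10% loss: 36 / (1 − 0.10) = 40 recruited, or about 40 / 2 = 20 per arm. The event counts and rates below are assumptions for illustration; the article gives none.

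- Fisher's exact test, two-sided, 4 of 20 versus 0 of 20: 2 × C(20,4) / C(40,4) = 2 × 4,845 / 91,390 = 0.106.
- The same test, 5 of 20 versus 0 of 20: 2 × C(20,5) / C(40,5) = 2 × 15,504 / 658,008 = 0.047.
- Chance of seeing at least one event among 20 women, 1 − (1 − p)^20: 18%, 33%, 64% and 88% for true risks p of 1%, 2%, 5% and 10%.

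When one arm has no events, a difference of about 25 percentage points (5/20) is needed before the test falls below 0.05. Counts by arm would therefore be descriptive.

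**The case against.** **The session log already captures other harms.** Recording the type of event makes little sense if only one type counts, and 3.1 covers any event during training. This stands. A reader might infer that the trial cannot detect non-muscular harms at all. The documents do not support that: a faint during a session, for example, would go on the trainer's sheet, and withdrawals with reasons are registered. What remains is that such an event would not count as an adverse effect under 2.9, and that the log covers only exercise-group sessions.

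**Section 2.9 itself promises more than its definition.** This also stands, and it makes the problem a contradiction to be resolved rather than a settled decision to ignore other harms.

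**A journal article condenses the full protocol.** This stands for case-report forms, seriousness grading and relatedness grading; their absence is not criticised here. It also means that silence about controls does not prove that their events go unrecorded. It does not excuse the definition, which is stated rather than left out.

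**A numerical size may be tempting.** Zero events in 20 women leaves a one-sided 95% upper limit of 1 − 0.05^(1/20) = 13.9%. That is correct arithmetic, but it reflects sample size alone and would be the same under a better definition. It does not measure this defect.

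**No event rates are given.** This is true, so nothing here claims that complications are more frequent with exercise.

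**Conclusion.** The point holds as one of definition and ascertainment. The only adverse-effect definition in the article is confined to muscle injury from training in the exercise group. It conflicts with the sentence before it in 2.9 and with 2.7.1.1 and 3.1. Beyond withdrawals and their reasons, the article describes no way to compare harms between arms.

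The size is qualitative. Non-muscular events in exercise sessions may be recorded but do not count. Exercise-group events outside sessions and after week 16, and all control-group events, have no stated capture short of withdrawal. The SHBG endpoint, the sample size and the efficacy analysis are untouched.

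The conclusion assumes that the article's definition is the one that will govern reporting. If the full protocol already sets a broader definition with the same collection in both arms, what remains is to correct the wording of 2.9. This is a worthwhile, inexpensive improvement and does not undermine the trial's efficacy result.

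**What to change.** Reconcile 2.7.1.1, 2.9 and 3.1 under one definition, and state how events are ascertained in both arms:

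- Define an adverse event as any untoward medical occurrence from randomisation to T3, in either arm.
- Collect it with the same questions in both arms at the existing post-operative visits and at T2 and T3. Sections 2.6.1 and 2.7.2 differ on whether there is a month 9 visit; settle this so that the collection points are fixed.
- Keep the answers away from the outcome assessors, who are blinded under 2.5. A self-completed form, or questions put by staff who take no part in outcome assessment, would do this.
- Report counts by arm, with seriousness and relatedness.
- Keep training-related musculoskeletal injury as a pre-named subset. Retain the trainer's session sheet as an additional source, and report what it adds separately, because it exists in one arm only.

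The cost is a short form at visits that already take place and modest data entry. The limitation should be stated in advance: with about 20 women per arm, the comparison of harms will be descriptive, without a formal claim of safety or of excess risk. The change should be made prospectively, because events that nobody asked about cannot be reliably recovered later.
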